#### 7.5.2. *Time to Death, Heart Failure Hospitalization, or Urgent HF Visit*

The composite outcome comprising the primary endpoint components (all-cause death, heart failure hospitalization, and urgent heart failure visits) will be analyzed as time to first event using Cox proportional hazards models. Results will be reported as hazard ratios (HRs) with corresponding 95% confidence intervals. Kaplan-Meier estimates will be used to display unadjusted time-to-event curves. All models will incorporate a random effect for participating site (frailty model) and will be adjusted for baseline left ventricular ejection fraction, sex, and age.

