#### **4.2. Randomization**

Patient allocation will follow a 1:1 ratio using a randomization list generated by a blockrand function, which generates random assignments. The probability of allocation to either CRT group will be equal, and stratification will be performed by center using variable block sizes of 4 and 6 patients. The randomization list will be uploaded into the REDCap system, allowing participating sites to access the assigned treatment group only once all eligibility requirements are fulfilled. Randomization will be conducted independently by the Research Support Center of the coordinating site at Hospital Moinhos de Vento, ensuring confidentiality throughout the process.

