### **4.5. Sample Size**

Assuming an incidence of all-cause mortality of 6.2% in both groups (based on the RAFT trial, which reported 20.8% over 40 months via linear extrapolation), a 1-year heart failure hospitalization rate of 5.85% (RAFT: 19.5% over 40 months), and a 1-year urgent visit rate for heart failure of 0.5% (DAPA-HF: 0.5 events per 100 patient-years), along with an estimated absolute increase in left ventricular ejection fraction (LVEF) of 16% in the intervention group versus 14% in the control group (a conservative estimate based on the His-Alternative study, which showed increases of 16% and 13%, respectively), and a standard deviation of 6.5 (based on values of 6 and 7 in each group from the same study), a sample size of 304 patients would be required to achieve 80% statistical power with a two-sided alpha of 5% (one-sided alpha of 2.5%) and a non-inferiority odds ratio bound  $<1.2$  for the upper limit of the 95% confidence interval, accounting for a 5% loss to follow-up (assumed to be non-informative dropouts for the purposes of sample size calculation).

Due to slower-than-anticipated enrollment and the publication of a meta-analysis during the conduct of the PhysioSync-HF trial (Gin et al., Heart Rhythm, 2023) showing a greater improvement in LVEF in the intervention group (2.70–5.18%) than the originally assumed 2%, the Steering Committee decided to recalculate the original sample size.

The updated calculation assumed a 3% difference in LVEF improvement between groups, favoring the intervention arm. Although the originally anticipated difference based on the His-Alternative study was also 3%, a more conservative estimate of 2% had been used in the initial sample size calculation due to limited available data at the time. With the revised assumptions, the required sample size was reduced from 304 to 180 patients, while preserving the non-inferiority margin of OR less than 1.2 for the upper bound of the confidence interval and 80% statistical power. All simulations were performed using 10,000 repetitions, as detailed in Appendix A.

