| HF hospitalization                                                                                          | xx (xx%)                             | xx (xx%)                                      | Hazard Ratio      | x.xx [x.xx - x.xx]               | x.xx [x.xx - x.xx]          | x.xxx   |
| Urgent visit for HF                                                                                         | xx (xx%)                             | xx (xx%)                                      | Hazard Ratio      | x.xx [x.xx - x.xx]               | x.xx [x.xx - x.xx]          | x.xxx   |
| Secondary ordinal outcome: all-cause mortality, HF hospitalization, urgent HF visit, and change in KCCQ-CSS | xx (xx)                              | xx (xx)                                       | Odds ratio        | x.xx [x.xx - x.xx]               | x.xx [x.xx - x.xx]          | x.xxx   |

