## APPENDIX A

Four power simulations were conducted using 10,000 iterations each, assuming a total sample size of 180 patients (90 per group) and odds ratio non-inferiority margins of 1.0, 1.1, 1.2, and 1.3.

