### *Parameters*

- Alpha (two-sided) 0.05
- Primary ordinal outcome: all-cause mortality at 12 months, heart failure hospitalization at 12 months, urgent heart failure visits at 12 months, and change in left ventricular ejection fraction (LVEF) at 12 months from baseline (categorized in 5% increments)
- Expected event rates (assuming independence)
- Mortality 6.24% in both groups
- Heart failure hospitalization 5.85% in both groups
- Urgent heart failure visits 0.5% in both groups
- Mean LVEF improvement 16% in the CSP group vs 13% in the BVP group
- Standard deviation of LVEF improvement 6.5
- 5% loss to follow-up

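### Table 1 asks for hazard ratios and a p-value for urgent HF visits alone, although the plan's own 0.5% rate implies about one event in the whole trial (minor; one component row)

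*Combined protocol and SAP*

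**What the plan says.** Table 1 (Section 7.6) lists, among the secondary outcomes, the composite of death, HF hospitalization and urgent HF visit, and then each component on its own line. The line "Urgent visit for HF" has the hazard ratio as effect measure and cells for an unadjusted effect, an adjusted effect, their 95% CIs and a p-value.

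Section 7.5.2 holds the plan's only Cox specification. It is written for the composite, but then says "All models will incorporate a random effect for participating site (frailty model") and adds adjustment for baseline LVEF, sex and age.

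The event rate is in Section 4.5, which assumes a "1-year urgent visit rate for heart failure of 0.5% (DAPA-HF: 0.5 events per 100 patient-years"), and in Appendix A: "Urgent heart failure visits 0.5% in both groups". On size, Section 4.5 states that "the required sample size was reduced from 304 to 180 patients". The Appendix A simulations were run "assuming a total sample size of 180 patients (90 per group").

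**The concern.** A hazard ratio comparing two arms needs at least one event in each arm to be finite, and many more to be informative. On the plan's own figures, urgent visits would fall well short of either.

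The analyst would then have two poor choices: print whatever the software returns (a zero or very large HR, an interval without meaning, an arbitrary p-value), or depart from the SAP after seeing the data. Nothing in the plan settles this in advance. It gives no minimum event count, no penalized or exact method, and no rule to describe only. Section 7.13 deals with missing data, not with few events.

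**Working it through.** **Inputs.** Urgent-visit rate 0.5% at one year in both arms (Section 4.5, Appendix A). N = 180, 90 per arm (Section 4.5, Appendix A), allocated 1:1 (Section 4.2). Loss to follow-up 5% (Appendix A). Clinical events are counted up to one year and 20 days after the index procedure (Section 7.14).

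**Reproducing the plan's figure.** The documents give no expected count of urgent visits. Their closest figure is the power of the primary analysis, 81.4% at margin 1.2. A simulation of an unadjusted proportional odds model (3,000 runs) with the Appendix A event rates, LVEF change of 16 versus 13 points, SD 6.5 and 5% loss gave 82.0%. That is within one point, so the inputs are read as the plan intends.

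**Expected urgent visits, both arms together.**
- N = 180: 180 × 0.005 = 0.90.
- After 5% loss: 171 × 0.005 = 0.86.
- N = 180, counted to one year and 20 days: 180 × 0.005 × 385/365 = 0.95.
- At the earlier target of 304: 304 × 0.005 = 1.52.

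**Distribution at N = 180.**
- P(no event) = 0.995^180 = 0.406.
- P(exactly one) = 180 × 0.005 × 0.995^179 = 0.367, so P(at most one) = 0.773.
- P(a given arm has none) = 0.995^90 = 0.637.
- P(both arms have at least one) = (1 − 0.637)² = 0.132, so P(at least one arm has none) = 0.868.
- P(five or more in total) = 0.002.

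With 171 patients, P(no event) is 0.424 and P(at least one arm has none) is 0.88.

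**Precision when the HR is finite.** With one event per arm, SE(log HR) ≈ √(1/1 + 1/1) = 1.41, and exp(1.96 × 1.41) ≈ 16. The 95% CI therefore runs from the estimate divided by about 16 to the estimate multiplied by about 16, before three covariates and a site variance are added.

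**If the 0.5% is too low.** The documents give no other rate, so these are assumed values at N = 180:

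| Assumed rate | Expected events | P(at least one arm has none) |
|---|---|---|
| 0.5% (plan) | 0.9 | 87% |
| 1% | 1.8 | 65% |
| 2% | 3.6 | 30% |
| 5% | 9.0 | 2% |

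At ten times the planned rate the HR would usually be finite, but nine events would still be too few for treatment, three covariates and a frailty.

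**Other event rows at N = 180.** Deaths: 180 × 0.0624 = 11.2. HF hospitalizations: 180 × 0.0585 = 10.5. Composite: 180 × [1 − (0.9376 × 0.9415 × 0.995)] = 21.9.

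**The case against.** The strongest reply is that this is one line of a table shell. Sections 3.2 and 4.4.2 list the composite, not urgent visits alone, as a secondary outcome, and no decision rests on this HR. Table 1 already shows counts and percentages by arm, so a reader would see one event against none beside the estimate, and an analyst could report it as not estimable. This reply stands as to weight, and is why the point is minor. It does not remove the defect: the cells are specified, and no rule allows them to be left empty.

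Four stronger readings are tempting, and the documents do not support them:

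- *Section 7.5.2 expressly orders an adjusted frailty model for urgent visits.* Its text names only the composite. The adjusted form for the component follows from its reference to all models together with Table 1's adjusted column. The unadjusted HR in Table 1 fails without that inference.
- *The plan leaves non-fatal HF events unreported.* Section 7.10 plans Poisson rate ratios for HF hospitalizations and urgent visits. Whether the two are pooled is not fully explicit. Table 1 lacks only a combined time-to-first-event row, and such a row would add about one event to the 10.5 expected HF hospitalizations, so it is not required. The Poisson models use the Cox covariates and are not a sparse-event rule.
- *The reduction in sample size caused the problem.* At 304 patients only about 1.5 events were expected, and the chance that at least one arm had none was 72%.
- *The HR can never be estimated.* At 0.5% there is a 13% chance that both arms have an event. The HR would then be finite, but not usable.

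**Conclusion.** The point holds and is minor. On the plan's own assumptions, the urgent-visit row of Table 1 would rest on about 0.9 events. There is a 41% chance of none at all and an 87% chance that the HR is zero, infinite or undefined. In the remaining 13%, the interval would be too wide to inform anyone. This rests on the 0.5% planning rate, which Section 4.5 takes from another trial, on events being independent between patients, and on 90 patients per arm. A moderately higher rate would make the HR finite more often but would not support the adjusted frailty model.

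The primary ordinal analysis, the cost outcome and the composite HR (about 22 expected events) are not affected.

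**What to change.** In Table 1, replace the two HRs and the p-value for urgent HF visits alone with the number and percentage per arm and an exact 95% CI for the risk difference. That interval exists whatever the counts. For scale, no events among 90 patients gives an exact two-sided 95% upper limit for that arm of 1 − 0.025^(1/90) = 4.0%.

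In Section 7.5.2, state that a component HR is shown only if a prespecified minimum number of events per arm is reached, and otherwise only the counts and the risk difference. Fix the number before the data are seen, bearing in mind that it also governs the other component rows. With a minimum of five per arm, for example, HF hospitalization at the planned 5.85% would qualify with a probability of only about 37%.

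The cost is a few lines of SAP and table wording. No data collection, sample size or other analysis changes, and what is lost is an HR that could not have been interpreted.

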## 7.6. Hierarchical Composite Outcome

### *Death, Heart Failure Hospitalization, Urgent HF Visit, and Change in KCCQ-CSS*

The hierarchical ordinal composite outcome comprising death, heart failure hospitalization, urgent heart failure visit, and change in KCCQ Clinical Summary Score (KCCQ-CSS) will be analyzed using the same proportional odds logistic regression model applied for the primary outcome. In cases of missing data, imputation for KCCQ-CSS will follow the same approach used for LVEF in the primary endpoint analysis. Non-inferiority testing will not be performed for this secondary outcome.

**Table 1.** Outcomes Assessed at 12 Months by Treatment Allocation

| Outcomes                                                                                                    | Biventricular
Pacing
[control] | Conduction
System Pacing
[intervention] | Effect
Measure | Unadjusted
effect
[95% CI] | Adjusted effect
[95% CI] | p-value |
|-------------------------------------------------------------------------------------------------------------|--------------------------------------|-----------------------------------------------|-------------------|----------------------------------|-----------------------------|---------|
| Primary outcome: heart failure–related clinical improvement                                          |                                      |                                               | Odds ratio        | x.xx [x.xx - x.xx]               | x.xx [x.xx - x.xx]          | x.xxx   |
| All-cause death                                                                                             | xx (xx%)                             | xx (xx%)                                      |                   |                                  |                             |         |
| HF Hospitalization                                                                                          | xx (xx%)                             | xx (xx%)                                      |                   |                                  |                             |         |
| Urgent Visit for HF                                                                                         | xx (xx%)                             | xx (xx%)                                      |                   |                                  |                             |         |
| Absolute change in LVEF at 12 months                                                                        |                                      |                                               |                   |                                  |                             |         |
| < -10%                                                                                                      | xx (xx%)                             | xx (xx%)                                      |                   |                                  |                             |         |
| [-10% a -5%)                                                                                                | xx (xx%)                             | xx (xx%)                                      |                   |                                  |                             |         |
| [-5% a 0%)                                                                                                  | xx (xx%)                             | xx (xx%)                                      |                   |                                  |                             |         |
| [0% a 5%)                                                                                                   | xx (xx%)                             | xx (xx%)                                      |                   |                                  |                             |         |
| [5% a 10%)                                                                                                  | xx (xx%)                             | xx (xx%)                                      |                   |                                  |                             |         |
| [10% a 15%)                                                                                                 | xx (xx%)                             | xx (xx%)                                      |                   |                                  |                             |         |
| [15% a 20%)                                                                                                 | xx (xx%)                             | xx (xx%)                                      |                   |                                  |                             |         |
| [20% a 25%)                                                                                                 | xx (xx%)                             | xx (xx%)                                      |                   |                                  |                             |         |
| [25% a 30%)                                                                                                 | xx (xx%)                             | xx (xx%)                                      |                   |                                  |                             |         |
| [30% a 35%)                                                                                                 | xx (xx%)                             | xx (xx%)                                      |                   |                                  |                             |         |
| ≥ 35%                                                                                                       | xx (xx%)                             | xx (xx%)                                      |                   |                                  |                             |         |
| Secondary outcomes                                                                                   |                                      |                                               |                   |                                  |                             |         |
| Mean direct medical cost per patient                                                                        | xx (x.xx - x.xx)                     | xx (x.xx - x.xx)                              | Mean difference   | x.xx [x.xx - x.xx]               | -                           |         |
| Composite of all-cause mortality, HF hospitalization, or urgent visit for HF                                | xx (xx%)                             | xx (xx%)                                      | Hazard Ratio      | x.xx [x.xx - x.xx]               | x.xx [x.xx - x.xx]          | x.xxx   |
| All-cause mortality                                                                                         | xx (xx%)                             | xx (xx%)                                      | Hazard Ratio      | x.xx [x.xx - x.xx]               | x.xx [x.xx - x.xx]          | x.xxx   |
| HF hospitalization                                                                                          | xx (xx%)                             | xx (xx%)                                      | Hazard Ratio      | x.xx [x.xx - x.xx]               | x.xx [x.xx - x.xx]          | x.xxx   |
| Urgent visit for HF                                                                                         | xx (xx%)                             | xx (xx%)                                      | Hazard Ratio      | x.xx [x.xx - x.xx]               | x.xx [x.xx - x.xx]          | x.xxx   |
| Secondary ordinal outcome: all-cause mortality, HF hospitalization, urgent HF visit, and change in KCCQ-CSS | xx (xx)                              | xx (xx)                                       | Odds ratio        | x.xx [x.xx - x.xx]               | x.xx [x.xx - x.xx]          | x.xxx   |

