### **7.4. Primary Outcome Analysis**

The primary outcome, an ordinal clinical endpoint related to heart failure, will be compared between groups using a mixed-effects proportional odds model. The model will include a random effect for recruiting site and will be adjusted for baseline left ventricular ejection fraction, sex, and age. The primary comparison will be based on the conditional effect of the intervention, interpreted as the effect averaged over the distribution of covariates included in the model. Participants who are lost to follow-up or have only vital status data available at 12 months, with no clinical outcome information after randomization, will be excluded from the primary outcome analysis. If a patient has no recorded clinical events (death, hospitalization, or urgent heart failure visit) but lacks an LVEF assessment within the specified time window, another LVEF measurement collected during follow-up will be used for imputation. If no LVEF data are available, the mean 12-month change in LVEF, pooled across both treatment groups, will be imputed.

The validity of the proportional odds assumption will be tested to support the interpretation of results. However, even if the assumption is not met, the primary outcome will still be analyzed using the proposed model, and the estimated odds ratio can be interpreted as a summary (average) effect across the ordinal scale (21). Analyses will be performed using the *rms* package in R (22).

The non-inferiority margin for conduction system pacing compared with biventricular pacing will be defined as an odds ratio  $<1.20$  for the upper bound of the confidence interval. If non-inferiority is demonstrated at the one-sided 2.5% significance level, superiority testing will be subsequently performed using the same model, preserving the overall alpha level.

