### **7.5. Secondary Outcome Analysis**

#### *7.5.1. Economic Outcomes and Cost Analysis*

To estimate the key secondary endpoint, a cost-minimization analysis will be conducted comparing the mean total direct medical cost per patient in the conduction system pacing (CSP) group versus the biventricular pacing (BiVP) group. Cost data will be consolidated in a patient-level database. To address missing data, a hierarchical imputation strategy will be employed, applying different methods based on the relevance of each variable and the presumed cause of the data being missing.

Key cost-driving variables will include device costs, time variables of the hospital resource use (serving as a primary *proxy* for overall resource consumption and labor resource use during the index hospitalization for the procedure), and costs associated with outcomes of interest.

A tolerance of up to 10% missing data will be allowed for time variables related to hospital resource use. If this threshold is exceeded, multiple imputation using *predictive mean matching* will be applied, based on covariates: enrollment site, baseline LVEF, sex, age, treatment group, and crossover occurrence. We will assume that missing data for these variables occur randomly at the patient level. No missing data are expected for device costs or outcome-related costs. For other cost-related variables with >10% missing data, median imputation will be used, assuming low impact on total costs and, consequently, on mean costs per treatment arm.

The primary economic endpoint will be presented as the mean cost difference between treatment groups. A generalized linear model with a log-link and gamma distribution will be used to test for significance, alongside non-parametric bootstrapping with 1,000 resamples to derive 95% confidence intervals. This approach accounts for the expected right-skewed distribution of cost data. Model adjustments may be made based on the final distribution of cost data at the end of follow-up. Additionally, median and interquartile ranges for cost outcomes will be reported by treatment group. This analysis will be based on the modified intention-to-treat (mITT) population, and the time frame will correspond to the duration of follow-up in the study.

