### **7.9. Other Secondary Outcomes**

Secondary outcomes assessed up to 12 months will be analyzed using linear regression models adjusted for baseline values. Treatment effects will be reported as mean differences with corresponding 95% confidence intervals. If a patient does not have a 12-month outcome assessment, an alternative measurement obtained during the study follow-up will be used. Patients with no measurements for a given variable during follow-up will be excluded from that specific analysis. **Table 2** provides a proposed summary of the secondary outcome effects.

**Table 2.** Comparative Analysis of Secondary Outcomes by Treatment Group

| Secondary Outcomes                                  | Biventricular Pacing
[control] | Conduction System
Pacing
[intervention] | Effect
Measure | Effect
[95% CI] | p-value |
|-----------------------------------------------------|-----------------------------------|-----------------------------------------------|-------------------|--------------------|---------|
| Echocardiographic Outcomes                   |                                   |                                               |                   |                    |         |
| Ejection fraction (%)                               | xx.x (xx.x)                       | xx.x (xx.x)                                   | Mean dif.         | x.xx [x.xx - x.xx] | x.xxx   |
| End-diastolic volume (ml)                           | xx.x (xx.x)                       | xx.x (xx.x)                                   | Mean dif.         | x.xx [x.xx - x.xx] | x.xxx   |
| Electrocardiographic and laboratory outcomes |                                   |                                               |                   |                    |         |
| Change in QRS duration (ms)                         | xx.x (xx.x)                       | xx.x (xx.x)                                   | Mean dif.         | x.xx [x.xx - x.xx] | x.xxx   |
| BNP (pg/ml)                                         | xx.x (xx.x)                       | xx.x (xx.x)                                   | Mean dif.         | x.xx [x.xx - x.xx] | x.xxx   |
| NT-proBNP (pg/ml)                                   | xx.x (xx.x)                       | xx.x (xx.x)                                   | Mean dif.         | x.xx [x.xx - x.xx] | x.xxx   |

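### The KCCQ-CSS composite is not adjusted for baseline KCCQ-CSS, and the cost and linear models leave out centre: a free gain in the secondary and exploratory analyses

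*Combined protocol and SAP*

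**What the plan says.** **Composite with KCCQ-CSS (7.6).** The outcome "will be analyzed using the same proportional odds logistic regression model applied for the primary outcome". Section 7.4 gives that model: proportional odds, a random effect for site, and "adjusted for baseline left ventricular ejection fraction, sex, and age". No baseline KCCQ-CSS term is named in either section. By contrast, natriuretic peptides (7.7), NYHA class (7.8) and the other continuous secondary outcomes (7.9) are each adjusted for their own baseline, as are the exploratory exercise-test outcomes (7.12).

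**Centre.** Under 4.2, "stratification will be performed by center using variable block sizes of 4 and 6 patients". Site is in the primary model (7.4), the Cox models (7.5.2), the 7.6 model because it takes over the primary one, and by reference the NYHA model (7.8). It is not named in 7.7, 7.9 or 7.12. For cost, 7.5.1 says "A generalized linear model with a log-link and gamma distribution will be used to test for significance", with bootstrap intervals for the mean difference. No covariates are listed, and Table 1 has a dash in place of an adjusted cost effect. The same section does use enrolment site to impute missing hospital-time variables.

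**Six-month visit.** Section 4.8 repeats the baseline measures at 6 and 12 months. Section 7.9 uses the earlier value only as a stand-in: "If a patient does not have a 12-month outcome assessment, an alternative measurement obtained during the study follow-up will be used". Sections 7.7 and 7.12 have the same rule. Patients with no follow-up value are excluded.

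**The concern.** The primary model's baseline LVEF term suits an outcome whose lowest tier is LVEF change. Carried unchanged into 7.6, it adjusts for a variable that is not part of that outcome and omits the one from which the change is measured. Change scores correlate negatively with their baseline, so leaving it out leaves avoidable noise in the tier that holds most patients.

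Omitting the factor used to stratify randomization discards between-centre variation that the design has already balanced. This matters most for cost, which is the main secondary outcome, carries a superiority objective, and plausibly differs between hospitals.

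Replacing a missing 12-month value with an earlier one treats it as a 12-month observation. If the treatment difference is still developing after month 6, the estimate is pulled toward the earlier difference, and the substituted value carries no extra uncertainty.

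**Working it through.** **1. The plan's own figure.** Inputs from Appendix A: two-sided alpha 0.05, 90 per group, mortality 6.24%, heart failure hospitalization 5.85%, urgent visits 0.5%, LVEF change 16 against 13 points with SD 6.5, and 5% loss (90 × 0.95 = 85.5, taken as 86 per arm). An unadjusted proportional odds simulation (4,000 runs) gave:

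| Margin | Appendix A | Simulated |
|---|---|---|
| 1.0 | 57.8% | 59.8% |
| 1.1 | 71.3% | 72.8% |
| 1.2 | 81.4% | 82.6% |
| 1.3 | 88.3% | 88.8% |

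The 304-patient design gave 79.4% against the stated 80%. The primary power is reproduced within about 2 points, and nothing below touches it. The documents give no power or precision figure for any secondary model.

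**2. Share of patients in the KCCQ-CSS tier.** With independent events, as Appendix A assumes: (1 − 0.0624) × (1 − 0.0585) × (1 − 0.005) = 0.9376 × 0.9415 × 0.995 = 0.878, about 88%.

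**3. Adding baseline KCCQ-CSS to the composite.** The documents give no SD, correlation, effect size or band width for KCCQ-CSS, so these are assumptions: SD 22, true difference 8 points, 5-point bands, 86 per arm, and the Appendix A event rates above the KCCQ tier. The proportional odds model was fitted with treatment alone and with treatment plus baseline KCCQ-CSS (600 runs per row). Efficiency is the ratio of (mean estimate / its SD)² with and without the baseline term.

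| Assumed correlation | Power without | Power with | Efficiency ratio |
|---|---|---|---|
| 0.4 | 36% | 45% | 1.34 |
| 0.5 | 45% | 52% | 1.25 |
| 0.6 | 51% | 56% | 1.19 |
| 0.7 | 63% | 67% | 1.13 |

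This is 13–34% more effective sample size. Site, LVEF, age and sex were left out of both fits.

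**4. Adding centre.** SE ratio = √(1 − share of variance explained by centre).
- Linear models, assumed ICC 0.01, 0.02, 0.05, 0.10: 0.995, 0.990, 0.975, 0.949. The SE is 0.5–5% lower.
- Cost, assumed share 10% or 30%: √0.90 = 0.95 and √0.70 = 0.84. The SE is about 5–16% lower. This is a linear-model formula, so it is only a guide for a gamma model with a log link.

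**5. Six-month data.** Let m be the fraction missing at 12 months but seen at 6, and r the correlation between the two visits (both assumed). The relative variance of the 12-month mean is 1 + [m/(1 − m)](1 − r²) in a repeated-measures model and 1/(1 − m) with complete cases.
- m = 0.05, r = 0.5: 1.039 against 1.053, SE ratio 0.994.
- m = 0.20, r = 0.8: 1.090 against 1.250, SE ratio 0.934.
- m = 0: both equal 1, so there is no gain.

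For bias under substitution, if the 6-month difference is a fraction f of the 12-month one and m is equal in both arms, the estimate is multiplied by 1 − m(1 − f):
- m = 0.05, f = 0.75: 0.9875.
- m = 0.20, f = 0.50: 0.90.

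The treatment difference shrinks by about 1–10%.

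**6. Deaths.** Section 7.14 covers transplantation for non-clinical endpoints, but the rules in 7.7, 7.9 and 7.12 do not mention death. At 6.24% of 180, about 11 patients die. If deaths are spread evenly over the year (assumed), 5 or 6 fall after month 6, and read literally those patients would contribute a 6-month value as their 12-month result.

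**The case against.** The strongest reply is that these are efficiency choices in analyses that do not decide the trial. The KCCQ-CSS composite is the last of ten additional secondary outcomes, the exercise-test outcomes are exploratory, and omitting a stratification factor generally makes inference conservative rather than invalid. That stands, and it sets the weight of the point.

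Some stronger readings are tempting but unsupported:
- **That the secondary models as a group ignore centre.** They do not. The sentence quoted from 7.6 is what brings the site effect into that model, and the Cox and NYHA models have it too.
- **That the KCCQ-CSS gain is 25–43% more patients.** This follows from (1 + ρ)/2 = 0.70–0.80 at correlations of 0.4–0.6, since 1/0.80 = 1.25 and 1/0.70 = 1.43. That formula compares baseline adjustment with an unadjusted change score for a continuous outcome. Section 7.6 is an ordinal model with event tiers above the change, and simulating it gives the smaller range.
- **That a repeated-measures model mainly buys precision.** With complete 12-month data it buys none. Section 7.14 also accepts late 12-month visits for these outcomes, which reduces substitution.
- **That such a model settles the handling of deaths.** It does not, because under missing at random it implicitly extrapolates beyond death. In 7.6 the issue does not arise, since death is the top tier.

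It is also fair that adding centre to a log-link cost model gives a cost ratio at a given centre, while the plan reports a mean difference. The fix has to deal with this.

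**Conclusion.** The point holds as a free improvement to secondary and exploratory analyses. The clearest part is the missing baseline KCCQ-CSS term, which departs from the plan's own practice for its other baseline-referenced outcomes. Its value, 13–34% in effective sample size, rests on assumed KCCQ inputs and correlations of 0.4–0.7. Centre is a modest gain in the linear models. It may be worth more for cost, but that depends on a variance share the documents do not give. The substitution rule is the lesser part: its cost is possible bias and overstated certainty, and its size depends on 12-month missingness and on how far the 6-month difference falls short of the 12-month one, neither of which is known. The primary analysis and its stated power stand.

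**What to change.** 1. **7.6:** add baseline KCCQ-CSS to the model's covariates, keeping the site effect.
2. **7.7, 7.9 and 7.12:** add centre to the linear models.
3. **7.5.1:** add centre to the cost model, draw bootstrap samples within centre and arm, and report the standardized mean cost difference (average predicted cost under each arm over all patients). Fill the adjusted cell for cost in Table 1.
4. **7.7, 7.9 and 7.12 (lesser):** replace the substitution rule with a repeated-measures model of the 6- and 12-month values, with baseline, visit, arm by visit and centre, reporting the 12-month contrast. State separately how deaths before 12 months are handled.

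The cost is SAP wording and analysis code, settled before the data are unblinded. Every variable is already collected, and no patients, visits or changes to the primary analysis are needed.
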